### Secondary outcomes

To assess the effect of FES and AFO treatment on gait over time, linear mixed-effects models will be performed, with gait analysis parameters as dependent variable and ‘walking aid’ (AFO, without AFO, FES, without FES) and ‘time’ [1 or 2] as fixed factors, and an interaction term ‘walking aid * time’ if applicable and a random intercept for subjects. A p-value of 0.05 is considered to be statistically significant in this analysis and Bonferroni correction for multiple comparisons is applied. Boxplot graphs will be made, showing the mean and standard deviation, as well as the individual data. This concerns the parameters: ankle dorsiflexion (in mid-swing and at initial contact), foot progression angle, foot clearance and push-off kinetics.

Nonparametric testing is expected to be appropriate for data with a source other than gait analysis, because of the lower number of observations (one measurement per time, instead of a mean of multiple measurements). This applies to the following parameters: dynamometry force, ankle range of motions based on physical examination, questionnaires (frequency of falling and toe drag, CPQoL, EQ5D-Y), physical activity and 6MWT distance. The Wilcoxon matched-pairs (signed ranks) test will be applied on the change-scores.

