### Objectives

Based on our previous systematic review [15], the overall hypothesis of the present study is that FES of the ankle dorsiflexors is an alternative to AFOs in daily life for some of the patients with CP. The primary objective is to show whether FES of the ankle dorsiflexors improves activities and participation of patients with unilateral spastic CP in daily life, measured with the Goal Attainment Scale (GAS) [18]. The secondary objective is to prove whether FES is effective at the level of body functions and structures, and activities (mainly measured with gait analysis and physical examination) and the tertiary objective is to collect relevant information on acceptability, characteristics for patient selection and cost-effectiveness to decide on implementation of FES in clinical practice. We hypothesize that the proportion of goal achievement (GAS scores) in the FES phase will be 30% higher than in the conventional phase and that FES is effective in improving ankle dorsiflexion by at least 5° during walking. Regarding characteristics for patient selection, we hypothesize that FES is effective in patients with a relatively flexible ankle joint and those who are relatively physically active, because the FES stimulation is only active during walking.

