## Methods

### Study design

The design of the study is a randomized crossover trial, consisting of a FES phase and a conventional therapy (mostly AFO) phase. It will be conducted at the Maastricht University Medical Center (MUMC+) in Maastricht, the Netherlands. The Medical Ethical Committee of the MUMC+ approved the study (METC azM/UM, study number 172033/NL63250.068.17). Figure 1 shows the flow chart for participants and the timing of the measurements. Four measurements will take place in total, at the start and end of every phase. Participants will take part in the study for 30 weeks. Patient recruitment and measurements will take place between August 2018 and August 2021.

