### Randomization and blinding

Subjects will be randomly assigned to start with either FES or conventional treatment. The randomization by blocks of four is based on even and uneven numbers, in envelopes created by the independent expert using www.random.org/sequences. Blocks of four are applied to ensure an equal distribution of the study phases over time which is important for FES device availability: of every four patients starting the trial, two will start with FES and two will start with the conventional therapy. The envelope will be opened once the patient has been included in the study, at the end of the intake appointment.

Blinding patients to the FES treatment is not possible, as most patients feel the electrical stimulation and obvious elicited muscle contractions are necessary for proper set-up. However, blinding of an assessor is possible: the physiotherapist (SF) that performs physical examination at every time point and assesses the GAS, will be blinded for the treatment phase. Patients and parents will be informed about the blinding procedure and instructed to take off the walking aid before visiting the physiotherapist.

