##### Procedure

Marker placement according to the HBM2 lower limb model with trunk is done by an experienced team [40]. For the kinematic model, functional calibration of the hip as described by Camomilla [42] is applied if the patient is able to perform the movements of the ‘star arc’: swinging the leg forward, oblique sideward, sideward and to the back, and finally swinging the leg in half a circle (flexion of 30°, half circumduction to extension of 30°, neutral position). These movements are performed in the hip and the knee is extended as much as possible. Functional calibration of the knee is applied performing a flexion-extension movement five times on each side.

Gait analysis is performed with and without the walking-aid (AFO or FES). At the first measurement, the comfortable walking speed is determined (with aid), by gradually increasing the speed of the treadmill with 0.01 m/s per second, starting at 0.5 m/s. The participant is asked three times to give a sign at the comfortable speed. The mean of the results is used for all gait analyses. For five conditions, 250 steps (125 gait cycles) are measured:Comfortable walking speed with walking aidFast (130% of comfortable) walking speed with walking aidComfortable walking speed without walking aidFast (130% of comfortable) walking speed without walking aidComfortable walking speed after fatigue protocol, with walking aid

Fatigue protocol: after condition 4 and a short break, the ‘fatigue protocol’ starts: the speed and incline of the treadmill gradually increase and the patient is asked to walk as long as possible wearing his/her walking aid (Table 3 shows the details). If the patient says to be really tired, the protocol is stopped: the treadmill returns to a flat position and the comfortable walking speed and the last 250 steps are measured. The patient is asked to give a score (0–10) on the children’s OMNI scale of perceived exertion for his degree of fatigue.(Appendix C, [43, 44]) The fatigue protocol is performed to investigate the influence of fatigue caused by walking on the gait pattern.

**Table 3 Tab3:** Details of the fatigue protocol

Stage	Time (minutes)	% walking speed of the comfortable speed	Incline (°)	Incline (%)
1	3 (0–2:59)	70%	2	3,5
2	3 (3–5:59)	85%	4	7
3	3 (6–8:59)	100%	6	10,5
4	3 (9–11:59)	115%	8	14
5	3 (12–14:59)	135%	10	17,6
6	3 (15–17:59)	140%	12	21,3
7	3 (18–20:59)	150%	12	21,3

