### Primary outcome

GAS scores will be dichotomized in to ‘goal achieved’ (scores 0 to + 2) and ‘goal not achieved’ (scores − 1 to − 3). The McNemar test (non-parametric) will be applied to test whether the proportions of goal achievement are significantly different between the FES and conventional phase. Raw GAS scores will also be provided. Beside an analysis including the patients who completed the study, an intention to treat analysis will be performed including the patients who discontinued the study as ‘goal not achieved’ (‘worst case analysis’). A *p*-value of 0.05 is considered to be statistically significant in this analysis.

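### The secondary gait model has only a patient intercept, so FES-versus-AFO and aid-on-versus-off share one error variance, and its time factor is undefined

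*Protocol article*

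**What the plan says.** Study design sets out the layout: "The design of the study is a randomized crossover trial, consisting of a FES phase and a conventional therapy (mostly AFO) phase". It adds: "Four measurements will take place in total, at the start and end of every phase". Under Randomization and blinding, "Subjects will be randomly assigned to start with either FES or conventional treatment", in blocks such that "of every four patients starting the trial, two will start with FES and two will start with the conventional therapy". The gait Procedure section has every child walk both with and without the current aid.

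Secondary outcomes then fixes the gait model. Walking aid enters as four states (AFO, AFO off, FES, FES off) and time as levels 1 and 2. There is an aid-by-time interaction "if applicable and a random intercept for subjects". No other random term is named, no term is called period or sequence, and the two levels of time are not explained. Bonferroni correction is applied. The model covers ankle dorsiflexion, foot progression angle, foot clearance and push-off kinetics.

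The primary analysis is separate: "The McNemar test (non-parametric) will be applied" to dichotomised goal attainment. The non-gait secondary outcomes use the matched-pairs Wilcoxon test on change scores.

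**The concern.** A patient intercept assumes that any two of a child's eight gait results are equally correlated, whether they come from one session or from sessions months apart. Two features of the trial speak against that.

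- Markers are placed and the joints calibrated for each session, so results from one visit share an error that other visits do not.
- The overall hypothesis is that "FES of the ankle dorsiflexors is an alternative to AFOs in daily life for some of the patients with CP". If response differs between patients, there is subject-by-aid variance. Each aid is used in one phase only, so this variance is also tied to phase.

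FES versus AFO carries this extra variance, while on versus off within a session is free of the visit part. With one pooled error, the first comparison looks too precise and the second too imprecise. These contrasts answer the questions on dorsiflexion, clearance and push-off.

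The undefined time factor adds a second gap. If it means start or end of phase, which is the natural reading given the visit schedule and the stated aim of assessing effects over time, the model has no period term. If it means period, start and end of phase are pooled.

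**Working it through.** The article gives no numerical result for the gait model, so there is no figure of its own to reproduce.

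**Inputs.** From the article: 22 completers (Sample size calculation), 2 phases x 2 visits x aid on/off = 8 values per child, and a random intercept only. Assumed, because the article gives no variances: residual variance 1, and subject-by-phase variance *p* and visit variance *v* each between 0 and 1.

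**Error variance the planned model estimates.** With a patient intercept, the residual mean square is the within-patient variance over 8 values (7 degrees of freedom). Four visits of two values contribute 2 x 3*v*/7, and two phases of four values contribute 4*p*/7:

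M = 1 + (6/7)*v* + (4/7)*p*

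**Variance of each contrast per child, model against truth.**

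- FES versus AFO (aid on), averaged over two visits: model M, truth 1 + *v* + 2*p*.
- FES versus AFO at one visit: model 2M, truth 2(1 + *v* + *p*).
- On versus off at one visit: model 2M, truth 2.

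**Ratio of model SE to true SE.**

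| *p* = *v* | M | FES-AFO, averaged | FES-AFO, one visit | On-off |
|---|---|---|---|---|
| 0 | 1.00 | 1.00 | 1.00 | 1.00 |
| 0.25 | 1.36 | sqrt(1.36/1.75) = 0.88 | sqrt(1.36/1.5) = 0.95 | sqrt(1.36) = 1.16 |
| 0.5 | 1.71 | sqrt(1.71/2.5) = 0.83 | sqrt(1.71/2) = 0.93 | sqrt(1.71) = 1.31 |
| 1 | 2.43 | sqrt(2.43/4) = 0.78 | sqrt(2.43/3) = 0.90 | sqrt(2.43) = 1.56 |

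If all the extra variance is subject-by-phase (*p* = 1, *v* = 0), the averaged FES-AFO ratio is sqrt(1.57/3) = 0.72. If it is all visit variance (*p* = 0, *v* = 1), that ratio is 0.96 and the on-off ratio is 1.36.

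**Simulated type I error** (nominal 5%, 11 children per sequence, no period effect, 6,000 runs per setting):

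| *p* = *v* | FES-AFO averaged, planned | On-off, planned |
|---|---|---|
| 0 | 5.0% | 4.8% |
| 0.25 | 8.9% | 2.4% |
| 0.5 | 10.6% | 1.2% |
| 1 | 12.0% | 0.4% |

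With a period term and the proper error level for each contrast, both stay between 4.5% and 5.5% in every setting. For FES versus AFO at one visit, ratios of 0.95 and 0.90 with a critical value of 1.98 give about 6.0% and 7.5%.

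**Second layout.** Replace *p* and *v* by a subject-by-aid variance equal to the residual. The truth for averaged FES-AFO is 2 + 1 = 3 and the model gives 1 + 6/7 = 1.86. The SE ratio is sqrt(1.86/3) = 0.79 and the error about 12%. Keeping the interaction does not cure this. The FES-AFO difference in start-to-end change has true variance 4 against 4 x 1.86 = 7.4 in the model, so its SE is about 36% too large.

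**Power.** With *v* = 1, *p* = 0 and an on-off effect of 0.5 residual SD averaged over two visits, simulated power is 38% under the planned model and 61% with a paired analysis.

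**Period.** The bias in an unadjusted FES-AFO difference is the period effect times (n1 - n2)/(n1 + n2). At 11/11 it is 0. Blocks of four put 25 children at 13/12, and three drop-outs, all from the smaller sequence, leave 13/9: 4/22 = 0.18 of the period effect. With a period effect of 1 residual SD and *p* = *v* = 0, the planned model's error for FES versus AFO is 2.6% at 11/11 (conservative) and 8.6% at 13/9.

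**The case against.** A reader might infer that the plan ignores the crossover. It does not: McNemar, matched-pairs Wilcoxon and the patient intercept all use the within-patient pairing. A reader might also infer that period is absent everywhere. For the gait model that cannot be asserted, because time is undefined. It can be said only that one of two needed factors is missing.

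Several limits on size are fair and stand:

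- All variance ratios are assumed, and at zero the plan is right.
- The 9-12% applies to FES versus AFO averaged over visits with the interaction dropped. At a single visit the error is close to nominal.
- The on-off error is conservative: it costs power and does not create false claims.
- With balanced sequences, omitting period costs precision only. A split as uneven as 14/8 cannot arise from 25 children in blocks of four without replacements.

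Two objections carry less weight. Bonferroni lowers the absolute rates but does not repair the SE. With six pairwise contrasts (0.05/6 = 0.83% each) and the subject-by-aid variance equal to the residual, the per-contrast error is about 3.5%, roughly four times its target. Fixed treadmill speed and an experienced marker team should hold visit variance down, but averaging about 125 cycles shrinks stride-to-stride noise and not visit error, so it may raise the ratio.

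An unseen analysis plan could add detail, but the random part is stated here and does not match the design described here.

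**Conclusion.** The point holds for the secondary gait models only. Their single random intercept cannot give correct standard errors for both kinds of contrast unless subject-by-phase (or subject-by-aid) and visit variances are zero. Under assumed variances of 0.25 to 1 times the residual, visit-averaged FES-versus-AFO intervals are about 12-22% too narrow and on-versus-off intervals about 16-56% too wide. The direction follows from the design; the size rests on variances the article does not give. The undefined time factor is a separate gap under either reading. Period bias arises only if completers are unbalanced by sequence.

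The primary McNemar test and the Wilcoxon tests are valid paired tests and are not called into question. This is worth correcting before analysis, but it does not threaten the primary conclusion.

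**What to change.** In the gait models:

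1. Define time as start or end of phase.
2. Add period (first or second phase) as a fixed effect.
3. Add random subject-by-phase (or subject-by-aid) and subject-by-visit intercepts, or an equivalent covariance structure, beside the patient intercept.

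The cost is one degree of freedom, two variance terms and a few lines of syntax, with no new data or patients. FES-versus-AFO intervals may widen, and on-versus-off intervals should narrow if visit variance is present. A period-adjusted version of the McNemar or Wilcoxon analyses is at most an optional sensitivity analysis.

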#### Characteristics for patient selection

We will identify patients in whom FES treatment was successful, based on the GAS. Next, we will review their age, MRI pattern, ankle angle (both during gait and physical examination), amount of spasticity, foot clearance, physical activity and 6MWT distance. Explorative logistic regression will be performed to see whether we can identify factors that are important for the chance of success of FES treatment.

#### Cost-effectiveness and cost-utility analysis

The McNemar test will be performed for the GAS outcome (goal achieved versus goal not achieved) for the cost-effectiveness analysis, just as in the main analysis. The Wilcoxon signed rank test will be performed for the EQ5D results for the cost-utility analysis. The time-horizon of both analyses is 3 months (i.e. referring to period before crossover). With a time-horizon of 3 months, no discounting is needed. Bootstrapping and sensitivity analyses will be performed to reflect respectively stochastic and deterministic uncertainty in the trial-based cost-effectiveness analysis. Cost-effectiveness acceptability curves will be constructed for a range of threshold values based on bootstrap analyses. Sensitivity analyses will be performed for price estimates and the perspective of the analyses. Quadrant graphs will be made showing the cost difference and effect difference, both for QALYs and GAS, including raw scores of the GAS and a line at the cut-off value for goal achieved/goal not achieved.

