**Methods:**

A randomized crossover trial will be performed on 25 children with unilateral spastic cerebral palsy. Patients aged between 4 and 18 years, with Gross Motor Functioning Classification System level I or II and unilateral foot drop of central origin, currently treated with AFO or adapted shoes, will be included. All participants will undergo twelve weeks of conventional treatment (AFO/adapted shoes) and 12 weeks of FES treatment, separated by a six-week washout-phase. FES treatment consists of wearing the WalkAide® device, with surface electrodes stimulating the peroneal nerve during swing phase of gait. For the primary objective, the Goal Attainment Scale is used to test whether FES improves activities and participation in daily life. The secondary objective is to prove whether FES is effective at the level of body functions and structures, and activities, including ankle kinematics and kinetics measured during 3D-gait analysis and questionnaire-based frequency of falling. The tertiary objective is to collect relevant information for clinical implementation, including acceptability using the device log file and side effect registration, cost-effectiveness based on quality adjusted life years (QALYs) and clinical characteristics for patient selection.

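### The economic analyses name paired tests but set their horizon as the period before crossover, when no child has yet had both treatments

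*Protocol article*

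**What the plan says.** The Statistics subsection on cost-effectiveness and cost-utility analysis fixes two tests and a period. For the GAS, with a pointer back to the main analysis: "The McNemar test will be performed for the GAS outcome". For the EQ-5D: "The Wilcoxon signed rank test will be performed for the EQ5D results for the cost-utility analysis". For the period: "The time-horizon of both analyses is 3 months (i.e. referring to period before crossover"). The next sentence uses the 3-month figure to explain why no discounting is applied. Bootstrapping, acceptability curves, sensitivity analyses and quadrant graphs follow.

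The main analysis that the GAS sentence points to is defined under Primary outcome: "The McNemar test (non-parametric) will be applied to test whether the proportions of goal achievement are significantly different between the FES and conventional phase". Under Secondary outcomes, the EQ-5D-Y is among the questionnaires covered by this rule: "The Wilcoxon matched-pairs (signed ranks) test will be applied on the change-scores".

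On the design, the Abstract says: "All participants will undergo twelve weeks of conventional treatment (AFO/adapted shoes) and 12 weeks of FES treatment, separated by a six-week washout-phase". Randomization and blinding adds that "of every four patients starting the trial, two will start with FES and two will start with the conventional therapy".

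**The concern.** Both named tests compare FES with conventional treatment within the same child and so need a result under each treatment. The stated period supplies only one. An analyst who follows the tests must use both phases; one who follows the horizon sentence must drop the second phase and compare two separate groups. The same paragraph can therefore lead to two different incremental effects with different uncertainty, and the choice could be made after the results are seen.

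What is at stake is the cost-effectiveness part of the tertiary objective. The Objectives section lists it, with acceptability and patient selection, among the information for deciding on implementation in practice. The section on cost-utility and cost-effectiveness says that the health effect is the GAS, the primary outcome measure. Under the horizon sentence, that effect would no longer be the estimate from the primary analysis.

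**Working it through.** **1. The contradiction (no arithmetic needed).**
- McNemar's test needs, for each child, goal achieved or not under FES and under conventional treatment (Primary outcome).
- The signed rank test needs a matched FES and conventional value for each child (Secondary outcomes).
- Each child has one treatment in the first 12 weeks and the other only after the six-week washout (Abstract; Randomization and blinding).
- Within-child FES-conventional pairs available before crossover: 0.

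A signed rank test of the EQ-5D at the start against the end of the first period could be computed. It would test change over time under one treatment, not FES against conventional treatment. The article names no unpaired test for the economic analyses.

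**2. The plan's own figures.** There is no sample size for the economic analyses. The only one is for the paired GAS comparison: 22 completers and 25 enrolled. The 22 cannot be reproduced exactly because the discordant proportion ψ is not given. With difference d = 0.30, n = (z_α√ψ + z_β√(ψ − d²))²/d² gives 24 two-sided at the smallest possible ψ of 0.30, and 22 one-sided at ψ = 0.35. Dropout of 14% gives 22/0.86 = 25.6, against 25 stated. The contradiction does not depend on these figures; only the group sizes below use 22 and 25.

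**3. Variance if the horizon sentence is followed.** Let s² be the common variance of an outcome and r the correlation between a child's two phases. The documents do not give r.
- Paired, 22 children: 2s²(1 − r)/22.
- Unpaired, 11 against 11 completers: 2s²/11.
- Ratio: (2/11) / (2(1 − r)/22) = 2/(1 − r).
- Unpaired, all 25 enrolled as 12 against 13: s²(1/12 + 1/13) = 0.1603s².
- Ratio to the paired analysis: 0.1603 / (0.0909(1 − r)) = 1.76/(1 − r).

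| assumed r | 11 v 11 | 12 v 13 |
|---|---|---|
| 0 | 2.0 | 1.76 |
| 0.5 | 4.0 | 3.5 |
| 0.7 | 6.7 | 5.9 |

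Only the first row needs no positive correlation. The other rows are illustrations.

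**4. The same loss on the GAS scale.** The achievement rates are not given, so the control rate was varied from 0.00 to 0.70 with a 30-point difference, two-sided 5% and the normal approximation for two independent proportions. With 11 per group, power runs from 0.281 (0.35 against 0.65) to 0.505 (0.00 against 0.30, or 0.70 against 1.00). With 12.5 per group it runs from 0.315 to 0.562. The normal approximation is rough at these group sizes.

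**The case against.** The best defence is that a time horizon is a duration. Three months matches one 12-week phase, and the next sentence uses the figure only to dispense with discounting. The reference to the main analysis and the matched-pairs rule for the EQ-5D-Y both point to a comparison of the two phases. On this reading a paired analysis was always meant and the bracket is loose wording. That may well be the intention, but the bracket explains the horizon as the time before crossover, and the benign reading is reached only by changing those words. This is also not detail left to a fuller document: the article states both the tests and the period, and they do not fit together.

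A second defence is that a first-period comparison is free of carryover, and the section on the wash-out phase accepts that FES effects may last a few weeks. This stands as a reason to keep that comparison as a sensitivity analysis. It does not make the paired tests possible within one period.

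A reader might infer more than the documents support:
- **That the economic analysis as a whole cannot be run.** Only the two named tests lack pairs. The bootstrap, acceptability curves and quadrant graphs can be produced from either set of data.
- **That the case for insurance coverage is undermined.** The Discussion ties coverage to clear guidelines for successful therapy, not to the cost-effectiveness result.
- **That a fourfold or larger variance penalty is established.** It depends on an r that no document gives.

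**Conclusion.** The contradiction is real and depends on no assumed number: the two named tests have no FES-conventional pairs in the period assigned to them, and nothing else in the article resolves this. Followed literally, the horizon sentence leaves an unpaired comparison of about 11 to 13 children per arm. The variance is then about 1.8 to 2 times that of the paired analysis at r = 0, and more if r is positive. This assumes equal variances in the two phases and 22 complete pairs. The GAS effect would come from a different comparison than the primary result it is said to reuse.

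The reach is limited to the tertiary cost-effectiveness objective. The primary McNemar analysis, the secondary analyses and the sample size are untouched.

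**What to change.** In the cost-effectiveness and cost-utility subsection, replace the bracketed words with a horizon of 3 months (12 weeks) per treatment phase. State that costs, EQ-5D-Y/QALYs and GAS are taken from both phases of each child. Both named tests then have their pairs, and the GAS effect is the one in the primary analysis. Add that the bootstrap resamples whole children, so that each child's FES-conventional pair stays together.

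A first-period-only comparison can be kept as a carryover-free sensitivity analysis, labelled as such and analysed with unpaired methods. Making it the main economic analysis would also be coherent, but the two paired tests and the reference to the main analysis would then have to go, at the loss of precision shown above.

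The cost is one sentence and a small change to the bootstrap code, provided that costs and EQ-5D-Y are collected in both phases. The Study design section places measurements at the start and end of every phase, and the matched-pairs rule implies EQ-5D-Y data from both. The article does not say when costs are recorded or at which visits the EQ-5D-Y is completed, so this should be confirmed before the wording is changed.
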